#### Questionnaires

Questionnaires will be administered at intermittent timepoints (Table 1). The PROMIS and EQ-5D-5 L will be used to assess health-related quality of life [15, 16]. Healthcare and societal costs will be evaluated using a selection of items relevant for this population of the medical consumption (iMCQ) and productivity (iPCQ) questionnaire [17]. If patients are able to complete questionnaires digitally, questionnaires are sent to the patient via Castor EDC.

**Table 1 Tab1:** An overview of the study visits and questionnaires administered during each visit

	Day 1	Day 3	Day 8	Day 15	Day 29	Day 60	Day 90	Day 180
CAUTI symptoms								
PROMIS								
EQ-5D-5 L								
iMCQ								
iPCQ								

### Outcome measures

The primary outcome is a recurrent CAUTI within 90 days after completion of antibiotic treatment, defined according to the same IDSA-based clinical and microbiological criteria used for inclusion. The pathogen does not have to be identical to the causative pathogen that was identified during the first episode.

All participants are instructed to contact the central study team should they experience CAUTI symptoms. Additionally, the physicians at the participating centres and general practitioners are instructed to report potential recurrences among participants.

Secondary outcomes:

Patient-related outcomes: 30-day mortality, health-related quality of life assessed using the PROMIS and EQ-5D-5L questionnaires.Process-related outcomes: time to resolution of CAUTI symptoms, time to resolution of fever, complications of catheter replacement and severity of the complications (5-level Likert scale).Resource-related outcomes: length of hospital stay, ICU-admission during hospital stay, healthcare and societal cost using a selection of items relevant for this population of the medical consumption (iMCQ) and productivity (iPCQ) questionnaire.

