**Methods and analysis:**

The REPLACE study is a multicentre, non-inferiority- randomized controlled trial designed to assess whether retaining the urinary catheter in patients with CAUTI is non-inferior to replacement in terms of the risk of a recurrent CAUTI within 90 days. Secondary outcome measures include 30-day mortality, health-related quality of life, time to resolution of CAUTI symptoms, complications related to catheter replacement and healthcare and societal costs. Patients aged 18 years or older with an indwelling catheter (transurethral or suprapubic) and CAUTI are eligible. CAUTI is defined according to the Infectious Diseases Society of America (IDSA) criteria. Three hundred patient will be randomised 1:1 to catheter retention (intervention group) or replacement (control group). In the intervention group, the catheter is not replaced. In the control group the catheter will be replaced within 3 days after start of antibiotic therapy. The primary outcome (recurrent CAUTI within 90 days) will be assessed for non-inferiority (margin of 10%).

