#### Exclusion criteria

A potential participant who meets any of the following criteria will be excluded from participation in this study:

Antibiotic treatment initiated more than 3 days prior to inclusion.Immunodeficiency: High-dose corticosteroid use (any equivalent of ≥ 20 mg prednisolone per day for > 4 weeks), severe primary immunodeficiency, organ transplant, neutropenia (absolute neutrophil count < 0.50 × 10⁹/L).Discontinuation of the indication for the indwelling catheter.A planned (routine) catheter replacement during antibiotic therapy.Contraindications for catheter replacement.Kidney catheters (nephrostomy or double-J catheter).Needing continuous bladder irrigations because of gross haematuria.Bladder stones.Pregnancy.A life expectancy of less than 90 days, as estimated by the treating physician.

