### Study interventions

Patients will be assessed for CAUTI according to standard practice of care. Potential participants will be screened against inclusion/exclusion criteria by the central study team. Eligible patients will receive written study information and provide written or remote informed consent before randomization.

After obtaining informed consent, participants will be randomized to either catheter replacement (control group) or catheter retention (intervention group). In the replacement group, the catheter will be replaced within 3 days of starting antibiotic treatment. All patients (men and women) will receive a 10-day course of antibiotics. The choice of antibiotic agent is at the discretion of the treating physician, except for nitrofurantoin, fosfomycin, and trimethoprim as these may be considered inferior for the treatment of CAUTI with systemic symptoms. Once culture and susceptibility results are available, therapy must be adjusted according to the EUCAST susceptibility criteria.

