### Data collection

Patients will be followed for a total period of 180 days, with seven telephone visits (Table 1). All follow-ups are done by a member of the central study team at the LUMC. Data will be collected on patient characteristics, symptoms, and urine analyses, and several questionnaires will be administered.

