#### Analyses of outcome measures

Descriptive statistics will be used to summarize baseline characteristics. In the primary analysis, the risk difference with (two-sided) 95% confidence interval will be computed to compare the differences in 90-day recurrence risk between the two treatment arms, in both the intention-to-treat population and the per-protocol population. Regarding the primary analysis, multiple imputation will be used to deal with missing outcome data (i.e. missing information regarding CAUTI recurrence). For the primary outcome, three sensitivity analyses will be performed to account for missing data. In the first sensitivity analysis, a complete case analysis will be performed. Additionally, a worst-case and best-case scenario analysis will be performed, in which patients who drop out of the study before 90 days will be included under the assumption that they experienced a recurrence (worst-case scenario) or no recurrence (best-case scenario), respectively.

The primary analysis will not take patient characteristics into account, as these are expected to be balanced between treatment groups (by randomization). In a secondary analysis, multivariable analysis will be performed including variables that are associated with recurrence of CAUTI.

The secondary outcome time-to-resolution will be analysed using Kaplan Meier survival analysis. For patient-related outcomes measures, such as PROMIS and EQ-5D-5 L, repeated measures analyses will be performed to compare these outcomes between the groups. For these outcome measures, multiple imputation will be used to deal with missing outcome data. Process and resource related outcome measures will be analysed in the per-protocol population. In addition, a cost-effectiveness analysis from a societal perspective with a 6-month time horizon and a budget impact analysis will be performed.

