### Implications and future directions

Current national and international guidelines, advice to change the catheter with a low level of evidence [1, 7, 8]. If this trial demonstrate that catheter retention is non-inferior to replacement, clinical practice could be standardized accordingly in future guideline updates. This may reduce the number of invasive procedures, decrease healthcare costs, lower material waste and alleviate patient burden without compromising safety. Conversely, if catheter retention is not found to be non-inferior, the results will strengthen the evidence base supporting current recommendations for catheter replacement and may improve adherence in clinical practice.

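### The only catheter-specific complication outcome is defined by the control-arm procedure and analysed per protocol, so it cannot give a balanced comparison of catheter-related complications

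*Protocol article*

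**What the plan says.** Under Outcome measures, the process-related secondary outcomes include "complications of catheter replacement and severity of the complications (5-level Likert scale"). The abstract gives the same scope: "complications related to catheter replacement and healthcare and societal costs".

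The two arms differ in exactly that procedure. The abstract says "In the intervention group, the catheter is not replaced", and Study interventions says "In the replacement group, the catheter will be replaced within 3 days of starting antibiotic treatment".

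Analyses of outcome measures states: "Process and resource related outcome measures will be analysed in the per-protocol population". The primary outcome, by contrast, is analysed in both the intention-to-treat and the per-protocol populations.

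Two further passages bear on which replacements could be counted. The exclusion criteria rule out only "A planned (routine) catheter replacement during antibiotic therapy", and Data collection says "Patients will be followed for a total period of 180 days". The article gives no time window for the complication outcome.

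Implications and future directions says that, if retention proves non-inferior, this may "decrease healthcare costs, lower material waste and alleviate patient burden without compromising safety".

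**The concern.** An outcome that compares harm between two strategies should be able to register harm from either. This one is tied to an exposure that allocation gives to one arm. Mechanical problems of a catheter left in place, such as blockage, leakage or an unplanned change, are not part of it, and no other listed outcome counts them.

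The analysis set adds to the imbalance. A retention patient whose catheter had to be changed early would, on a natural reading, have departed from the allocated strategy and could leave the per-protocol population. Those are the patients most informative about problems with retention.

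The article's Background names procedural complications as a main reason why clinicians retain catheters, so this result is likely to be read as evidence on catheter-related harm. If a non-inferiority finding is published beside it, readers may take it as support for the safety statement, which it cannot supply.

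**Working it through.** **Plan's own figures.** The article states no figure for this outcome. The sample size section gives 150 per arm, a 10% recurrence rate in both arms, a 10% margin, one-sided alpha 2.5% and power of about 80%. That power reproduces: the standard error is √(2 × 0.10 × 0.90 / 150) = 0.0346, and Φ(0.10/0.0346 − 1.960) = 82.3% by the simple normal approximation. The present point does not touch this calculation.

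**Inputs for the complication outcome.**
- n = 150 per arm, from the sample size section. The per-protocol number may differ.
- c = complication risk per replacement. The documents give none, so 2%, 5% and 10% are assumptions.
- x = share of retention patients replaced anyway and still counted. This is also assumed: 0, then 5% to 20%.

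**Formulas.** Expected events are n·c in control and n·c·x in retention. The risk difference (retention minus control) is c·x − c = −c(1 − x). This is negative for every c > 0 and x < 1. The rate of blockage or leakage in a retained catheter does not appear in it. Such a problem matters only if it leads to a counted replacement, and then only through x.

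| c | Control events | Retention events, x = 0 | Difference, x = 0 | Retention events, x = 5% to 20% | Difference, x = 5% to 20% |
|---|---|---|---|---|---|
| 2% | 3.0 | 0 | −2 points | 0.15 to 0.6 | −1.9 to −1.6 points |
| 5% | 7.5 | 0 | −5 points | 0.375 to 1.5 | −4.75 to −4.0 points |
| 10% | 15.0 | 0 | −10 points | 0.75 to 3.0 | −9.5 to −8.0 points |

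**Later routine changes.** Suppose every patient in both arms also has one later routine replacement that counts. The retention risk is c and the control risk is 1 − (1 − c)². This gives 2.0% v 4.0%, 5.0% v 9.75% and 10.0% v 19.0% (retention v control). Retention is no longer at zero, but the expected direction is unchanged.

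**Effect of the per-protocol set.** If retention patients with an early change are excluded, x moves towards 0 and the difference towards −c, the largest gap in the table.

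**The case against.** The strongest reply is that harm from retention is well covered elsewhere. The main danger of leaving the catheter in place is persistent or recurrent infection. Recurrence is the primary outcome and is compared in both populations. Mortality at 30 days, time to resolution of symptoms and of fever, PROMIS, EQ-5D-5L, hospital stay and ICU admission can also go against retention. This stands. A reader might infer that the trial's whole harm comparison can only favour retention; the documents do not support that.

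Three other readings go too far:
- A reader might infer that the retention arm's count must be zero. No window is stated, follow-up runs to 180 days, only routine changes planned during antibiotic therapy are excluded, and the per-protocol population is not defined in the article. Later replacements, and complications from them, are possible in that arm.
- A reader might infer that a safety conclusion is already planned. The Discussion text is conditional and follows from non-inferiority on recurrence; it is not linked to the complication outcome. No between-arm test of that outcome is stated either, and it may be meant as a description of procedural risk.
- A reader might want to put a figure on net harm. The documents give no rate of mechanical problems in either arm, and a newly placed catheter can also block, so no net figure can be derived.

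It can also be said that recording blockage or leakage is ordinary adverse-event capture, which an article leaves to the full protocol. That is fair, and nothing here claims that such events go unrecorded. The objection is to what the article does state: a named secondary outcome with a one-sided definition, assigned to a per-protocol analysis. Even as a description, it cannot show the balance of catheter-related complications between the strategies.

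**Conclusion.** The point holds for this one secondary outcome. Under the assumptions used, its expected difference favours retention by 1.6 to 2 points at a 2% risk per replacement, by 4 to 5 points at 5%, and by 8 to 10 points at 10%.

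The direction rests on two assumptions: retention patients have fewer counted replacements than control patients, and the risk per replacement is similar in both arms. If only the index period counts and 20% of retention patients are replaced, the risk per replacement in that arm would have to exceed 1/0.20 = 5 times the control risk to reverse the sign. That retention patients with an unplanned change are dropped is a possibility, not a stated rule.

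This is a low-cost improvement, not an error in the primary analysis. It matters for what may be said about catheter-related safety alongside a non-inferiority result.

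**What to change.** Redefine the outcome as catheter-related complications in both arms, over the same stated window. Include procedural complications and, for example, blockage, leakage, bleeding, and unplanned change or removal. Use the same 5-level severity scale for all of them and compare by randomised arm, so that patients whose catheter was changed against allocation stay in the comparison. Keep complications of replacement as a descriptive sub-item, reported among patients who had a replacement.

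The cost is a changed outcome definition and a few extra items at the seven telephone visits already planned. Patients already followed may have to be completed from their records, with some loss of detail on milder events. The primary test, margin and sample size stay as they are.

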### Statistical analysis

#### Sample size

It is planned to recruit 300 participants (150 in each treatment arm). For both groups, we assume a recurrence rate of 10% [18] within 90 days after start of antibiotic therapy. Analyzing the data as a non-inferiority study, taking a non-inferiority margin of 10%, and a (one-sided) type-I error rate (alpha) of 2.5%, a study with 300 participants would have a power of approximately 80%. A power of 80% would indicate that the likelihood is 80% that the upper-limit of the 95% confidence interval for the 90-day risk difference will exclude a difference of 10% in favour of the control (replacement) group. To account for post-randomization exclusions, we plan to randomize 400 participants.

An interim analysis of the overall recurrence rate will be performed after 50% of the initially planned sample size has completed 90 days of follow-up. The interim analysis will not assess treatment effectiveness, and no early stopping for efficacy or futility is planned. The sole purpose of this interim analysis is to evaluate whether the observed overall recurrence rate aligns with the assumptions used for the sample size calculation. If the recurrence rate is found to be below 7.5%, the project group will consider whether an increase in the sample size is warranted.

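### The interim sample-size trigger runs opposite to the trial's own calculation: with a fixed 10-point margin, a low recurrence rate raises power, yet only a low rate prompts a review and no trigger is stated for a high one

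*Protocol article*

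**What the plan says.** All of this is in the protocol article, Statistical analysis, under Sample size, unless noted.

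- Size: "It is planned to recruit 300 participants (150 in each treatment arm").
- Event rate: "For both groups, we assume a recurrence rate of 10% [18] within 90 days after start of antibiotic therapy".
- Margin and error: "taking a non-inferiority margin of 10" percent, with "a (one-sided) type-I error rate (alpha) of 2.5" percent.
- Criterion: success means that "the upper-limit of the 95% confidence interval for the 90-day risk difference will exclude a difference of 10" percent. Analyses of outcome measures confirms that the primary comparison is a risk difference with a two-sided 95% interval. The margin is thus absolute and does not move with the event rate.
- Stated power: "a study with 300 participants would have a power of approximately 80" percent.
- Allowance: "To account for post-randomization exclusions, we plan to randomize 400 participants".
- Interim look: made at half of the initially planned sample size, on the overall recurrence rate, with no assessment of treatment effect and no early stopping. Its only purpose is to compare the observed rate with the planning assumption. The one stated consequence is: "If the recurrence rate is found to be below 7.5%, the project group will consider whether an increase in the sample size is warranted".

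No trigger is given for a rate above 10%, and no rule links the margin to the observed rate.

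**The concern.** For a common rate p below 50%, the variance of a risk difference grows with p(1−p). With the margin held at 10 points, a lower rate gives a narrower interval and more power, and a higher rate does the reverse. A trigger on low rates suits a design driven by event counts or a relative effect, which this is not.

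Two things are at stake. If the true rate is above 10%, the trial can pass its only stated check and finish with less power than planned. The Implications section says that failing to show non-inferiority would strengthen the case for replacement, so lost power could be misread as evidence. If the true rate is low, the group is invited to discuss adding patients whom the fixed-margin calculation does not require.

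**Working it through.** **Inputs** (Sample size section): 150 per arm, equal true rates p, margin 0.10 on the risk difference, one-sided alpha 0.025, target power 80%.

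**Step 1: reproduce the stated power.** Power = Φ(0.10/√(2p(1−p)/150) − 1.96). At p = 0.10 the standard error is √(0.18/150) = 0.0346, so power = Φ(2.887 − 1.960) = Φ(0.927) = 82.3%. Exact binomial enumeration gives 81.9% with a Wald interval and 80.3% with Newcombe or Farrington-Manning limits. The Farrington-Manning asymptotic formula gives 78.8% and a continuity-corrected Wald 76.9%. The stated figure of about 80% is sound at the assumed rate.

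**Step 2: vary the rate, margin fixed.** Patients per arm for 80% power = (1.960 + 0.842)² × 2p(1−p)/0.10², which is about 1570 × p(1−p), rounded up.

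| Common rate | p(1−p) | Power at 150/arm, normal approx. | Power, exact score | Per arm for 80% (normal approx.) |
|---|---|---|---|---|
| 5% | 0.0475 | 97.8% | 95.5% | 75 |
| 7.5% | 0.0694 | 90.8% | 88.3% | 109 |
| 10% | 0.0900 | 82.3% | 80.3% | 142 |
| 12.5% | 0.1094 | 74.5% | 73.0% | 172 |
| 15% | 0.1275 | 67.9% | 66.8% | 201 |
| 20% | 0.1600 | 58.1% | 57.6% | 252 |

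The direction is the same under either method. At the 7.5% trigger the trial already has 88 to 91% power, and 2 × 109 = 218 patients would give 80%. At 15% it would need 2 × 201 = 402 analysable patients.

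**Step 3: break-even rate.** Setting 150 = (1.960 + 0.842)² × 2p(1−p)/0.01 gives p(1−p) = 0.0956, so p is about 10.7% on the normal approximation. With exact score limits, power at 10% is already only 80.3%, so the break-even lies closer to 10%.

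**Step 4: the 400 randomised.** The extra 100 are set aside for post-randomisation exclusions. If none were excluded (200 per arm), power would be 80.0% at 15% and 70.5% at 20%. That is a ceiling.

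**Step 5: how often the trigger is met.** The article gives both 300 and 400, so half of the planned size could mean 150 or 200 patients.

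- True 10%, look at 150: P(X ≤ 11) = 17.1%.
- True 10%, look at 200: P(X ≤ 14) = 9.3%.
- True 5%, look at 150: P(X ≤ 11) = 92.6%, where power is about 97%.
- True 15%, look at 150: P(X ≤ 11) = 0.3%, where power is about 68%.

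**Step 6: the break-even as a trigger.** A pooled rate above 10.7% in 150 patients means 17 or more events. At a true 10%, P(X ≥ 17) = 33%. The break-even rate is therefore a poor action threshold.

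**The case against.** The strongest reply is that the rule is mild. It commits the group only to considering an increase. If the group repeats its own calculation at a rate under 7.5%, it will find that none is needed. The stated purpose, checking whether the rate agrees with the assumption, covers both directions, so a high rate would be seen. These points stand, and they rule out two readings that a reader might infer: that the plan obliges the trial to recruit unneeded patients, and that it would ignore a high rate. The documents show only that no trigger is stated for a high rate. Nor does power collapse above 10%: the loss is gradual, about 79% at 11% and 74% at 12.5%.

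A second reply is that a low-rate review has a rationale, because a 10-point margin is lenient at a low base rate (at 5% it allows a tripling to 15%). That is true, but more patients at the same margin do not cure it. A low-rate trigger would make sense if the margin were tightened; as an illustration, a 5-point margin at a 5% rate needs 299 per arm. The article states no such link.

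A third reply is that 400 are randomised. If fewer than 100 are excluded, power at high rates is better than tabulated, up to the ceiling in step 4. This softens the size of the problem but does not change the direction of the rule.

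Finally, the analysis plan might say more. The point concerns a rule that is printed in the article and is wrong as printed, so it does not depend on missing detail.

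**Conclusion.** The point holds. The only stated trigger runs against the fixed-margin calculation on which the sample size rests, and no trigger is stated on the side where power is lost. Power at 150 per arm is about 91% at the trigger rate, against 68% at 15% and 58% at 20%, where nothing is prespecified.

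These figures assume equal true rates, 150 analysable patients per arm and a margin held at 10 points. Exact score methods lower them by up to about 2.5 points without changing their order. The chance-firing figures depend on whether the look is at 150 or 200 patients.

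A reader might infer that the trial is underpowered as planned or that its type-I error is affected. Neither follows: the stated power is reproduced at 10%, and the look is described as not assessing treatment effect and stops nothing. The harm is limited to undetected loss of power or a misdirected discussion about enlarging the trial.

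**What to change.** Before the interim look:

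1. Replace the low-rate trigger with re-estimation of the required sample size from the arm-blind pooled rate at the 10-point margin, so that action is considered when that rate is materially above 10%.
2. Choose the threshold with its chance of firing in mind, avoiding a cut-off at the break-even rate (step 6), and state the number of patients at the look.
3. State the action. The minimum is to restate the achievable power. Enlargement within a stated cap is an option.
4. At a low rate, make no increase at the same margin. Either drop the low-rate trigger or justify it with an explicit rule that tightens the margin. Report the relative risk with its interval, because the 10-point margin is lenient there.

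The cost is a few sentences in the protocol or analysis plan. Restating power needs no patients. Enlargement does: at a true 15%, 402 analysable patients instead of 300, plus the allowance for exclusions.
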